## Abstract

**Background:**

Views on advance care planning (ACP) has shifted from a focus solely on treatment decisions at the end-of-life and medically orientated advanced directives to encouraging conversations on personal values and life goals, patient-caregiver communication and decision making, and family preparation. This study will evaluate the potential utility of a video decision support tool (VDST) that models values-based ACP discussions between cancer patients and their nominated caregivers to enable patients and families to achieve shared-decisions when completing ACP’s.

**Methods:**

This open-label, parallel-arm, phase II randomised control trial will recruit cancer patient-caregiver dyads across a large health network. Previously used written vignettes will be converted to video vignettes using the recommended methodology. Participants will be ≥18 years and be able to complete questionnaires. Dyads will be randomised in a 1:1 ratio to a usual care (UC) or VDST group. The VDST group will watch a video of several patient-caregiver dyads communicating personal values across different cancer trajectory stages and will receive verbal and written ACP information. The UC group will receive verbal and written ACP information. Patient and caregiver data will be collected individually via an anonymous questionnaire developed for the study, pre and post the UC and VDST intervention.

Our primary outcome will be ACP completion rates. Secondarily, we will compare patient-caregiver (i) attitudes towards ACP, (ii) congruence in communication, and (iii) preparation for decision-making.

**Conclusion:**

We need to continue to explore innovative ways to engage cancer patients in ACP. This study will be the first VDST study to attempt to integrate values-based conversations into an ACP intervention. This pilot study’s findings will assist with further refinement of the VDST and planning for a future multisite study.

**Trial registration:**

Australian New Zealand Clinical Trials Registry No: ACTRN12620001035910. Registered 12 October 2020. Retrospectively registered.

**Supplementary Information:**

The online version contains supplementary material available at 10.1186/s12904-021-00794-3.

## Background

All people have the right to make decisions about how they are cared for in the future. However, many lose this ability as they approach the end-of-life (EOL). Advance care planning (ACP) may provide an avenue to ascertain patients’ wishes in circumstances where they are unable to articulate them due to a loss of capacity [1, 2]. A recent multidisciplinary panel of ACP experts defined ACP “as a process that supports adults at any age or stage of health in understanding and sharing their personal values, life goals, and preferences regarding future medical care” [3]. Elucidating ACP enhances desirable EOL outcomes, including patient-caregiver confidence and satisfaction [4, 5], quality of death [2, 6], and family bereavement experiences [6]. ACP requires reflection and communication and is an iterative process that is both individualized and shared [7, 8]. Contemporary views have shifted from ACP focused solely on treatment decisions at the EOL and medically orientated advanced directives. It instead encourages conversations that communicate personal values and life goals to support patient-caregiver communication and decision-making [9], family preparation [10, 11], and the actualization of ACP’s through innovative interventions [12].

Specific ACP challenges are recognized in cancer care, with ACP in cancer limited in completion, scope, timing, and translation into desired care [13]. Patients commonly prefer discussions later in their cancer journey [14], initiated by their treating physicians, and prefer multiple opportunities for conversations [13, 15]. The physician is required to strike a balance between engendering hope and maintaining truthful communication that ideally incorporates prognostic information [16]. Low uptake may be associated with standardized programs failing to capture the complex social and emotional nuances experienced by the cancer patient and their family across ages, genders, cancer types, and trajectories [17].

Cancer is a family experience, and the heightened involvement of family caregivers in cancer ACP studies is welcomed [10, 18]. Fluctuating awareness of treatment goals among cancer patients and their primary caregivers and the lack of concordance in patient-caregiver communication in cancer impacts effective care [19, 20]. However, cancer care provision in the ambulatory setting has augmented the opportunity to align patient-caregiver communication to support patient-caregiver dynamics, coping, adjustment, and psychological well-being [21]. Patients’ and caregivers’ assertive behaviours alongside caregiver presence in cancer consultations can reinforce patients’ participation in care discussions. This then allows for the triadic alignment of goals between the patient, caregiver, and health professionals [22, 23]. Such opportunities may then allow us to explore how individual and shared family values may influence treatment decision-making.

ACP interventions involving cancer patients on the whole, have increased ACP documentation rates from 15 to 30%–40% but failed to achieve EOL care consistent with patients’ preferences [24]. It is increasingly accepted that patient’s values and beliefs are the best predictors of the choices they make relating to end of life goals and treatment decisions [25], leading to ACP research exploring EOL values and the development of values-based ACP documents [26, 27]. Incorporating values directives into ACP removes the emphasis of decisions on specific medical interventions, such as cardiopulmonary resuscitation and intubation. It allows a focus on questions related to personal and family relationships, future concerns related to health, spiritual care, and end of life contingency planning [26]. In maturing the research around EOL values, tools such as decision aids with designs responsive to diverse philosophical perspectives are needed, with the flexibility to change as patients gain experience with their personal illness course.

Video decision aids or Video Decision Support Tools (VDST) incorporating video vignettes in ACP are garnering considerable interest amongst academics, clinicians, and policymakers due to their ability to dynamically depict diminishing health states and the nature of different treatment options in culturally and ethnically congruent manners. A recent systematic review and meta-analysis of 10 randomised controlled trial’s (RCT’s) (2220 patients) examining VDST to assist ACP found that patients who use a VDST were less likely to indicate a preference for cardiopulmonary resuscitation (pooled RR, 0.50; 95% CI 0.27–0.95) and acquired improved ACP knowledge [12]. Only four trials reported data on completion of advance directives, with no studies examining the effect on improved preparation in decision-making or patient-caregiver communication.

This study aims to build on the paucity of research exploring conversations about individual values between cancer patient-caregiver dyads and examining their impact on EOL decision-making and ACP. We hypothesize that patients exposed to a VDST that models values-based ACP discussions between patient-caregiver dyads can be an innovative approach to promote ACP in cancer. This study aims to evaluate the effect of a VDST depicting values communication on rates of completion of ACP, attitudes towards ACP, congruence in communication and preparedness for decision-making. The protocol is outlined according to the SPIRIT (Standard Protocol Items: Recommendations for Interventional Trials) guidelines [28].

## Methods / design

### Study design and setting

This is a prospective, RCT with two parallel groups receiving usual care (UC) or VDST intervention forms part of a research program of ACP in cancer developed in accordance with the Medical Research Council framework for developing complex interventions [29]. In this exploratory study, participants are enrolled in the study as dyads – a patient diagnosed with incurable cancer and a nominated caregiver. In this study, caregivers are defined as a relative, partner, or friend who has a significant relationship with the patient and provides them with social, psychological, and physical assistance [30].

The study will be conducted across three sites in a large not for profit health network Melbourne, Australia. ACP in the hospital is governed by legislation through a jurisdictional Medical Treatment Planning and Decision Act 2016 [31]. The Act establishes a single framework for medical treatment decision-making for people without decision-making capacity that ensures that people receive medical treatment consistent with their preferences and values. Standard forms under the Act allow for the appointment of a Medical Treatment Decision Maker (MTDM) and Support Person and completion of a Values and Instructional Directive (Table 1).

**Table 1 Tab1:** Components of an advance care plan/directive

**Appointment of Medical Treatment Decision Makers and Support Persons**	
Medical Treatment Decision Maker*	A medical treatment decision maker has the legal authority to make medical treatment decisions on behalf of the patient if they do not have the decision-making capacity to make a decision. It is the first person the patient listed who is reasonably available, and willing and able to make a decision. Only adults can appoint a medical treatment decision maker.
Support Person	A support person can access, or help a patient access health information relevant to their medical treatment. The support person does not have the power to make medical treatment decisions on the patient’s behalf.
Medical Enduring Power of Attorney	A medical enduring power of attorney authorizes another person to make decisions about medical care and treatment on a patient’s behalf if they do not have the decision-making capacity to make a decision. The person making the medical enduring power of attorney is called the appointer, and the person who accepts the appointment is the agent.
**Values and Instructional Directives**	
Values Directive	A medical treatment decision maker is legally required first to consider the patient’s values directive when making decisions about their medical treatment.
Instructional Directive	An instructional directive is legally binding and communicates the patients’ medical treatment decision(s) directly to their health practitioner(s). It is recommended that the patient consult a medical practitioner if they choose to complete an instructional directive. • An instructional directive will only be used if the patient does not have the decision-making capacity to make a medical treatment decision. • The medical treatment decisions in the instructional directive take effect as if the patient has consented to, or refused to, begin or continue medical treatment. • If any of the statements in an Instructional Directive are unclear or uncertain in particular circumstances, it will become a values directive. • In some limited circumstances set out in the Act, a health practitioner may not be required to comply with an instructional directive. • The patient has the option of consenting to or refusing future medical treatment.

*The appointment of a MTDM replaced the appointment of a Medical Enduring Power of Attorney (MEPOA). A MEPOA appointment made before the law changed is recognized under the new Act

### Participants and recruitment

Patients with non-curable cancer will be recruited from the oncology and palliative care across different sites at the health network. Eligible patients will have a diagnosis of incurable cancer and not have completed current ACP documents. Patients who have previously only appointed a MEPOA will be eligible to participate. Both patients and caregivers will have to be over the age of 18, be sufficiently proficient in English, and have a clinically determined prognosis of a minimum of 8 weeks post-randomization. Patients and caregivers will be ineligible for the trial if they are deemed too unwell and are unable to give informed consent due to cognitive or language barriers.

### Development of video vignettes

The video vignettes will be developed from the findings of our preliminary research into ACP in cancer patients [7, 10]. These studies incorporated the use of written vignettes, depicting a cancer patient’s scenarios across four stages of the cancer trajectory. In our preliminary studies, patients were depicted as declining in function and requiring various levels of care [7, 10, 32, 33]. Vignettes were presented to patients and caregivers in interviews and focus groups to elicit views on ACP and subsequently to patient-caregiver dyads as part of a facilitator-guided intervention in a feasibility study [32]. Qualitative secondary analysis on the use of written vignettes revealed that the vignettes provide a platform to promote values-based conversations and may facilitate congruence in communication between the patient and caregiver [33].

In developing the video vignettes, the research team will adhere to suggested guidelines for the preparation of scripted video vignettes which are 1) deciding on the appropriateness of the use of video vignettes, 2) developing a valid script, 3) designing valid manipulations, 4) converting written scripts to video, 5) administering the videos [34].

The written script will be developed by senior clinicians, drawing from cases used in previous studies [7, 10]. Manipulations will include representation of patient-caregiver dyads from differing ages, gender, stages of illness and relationships e.g. older patient and spouse/partner; middle-aged patient and sibling; younger patient and friends). This, as well as settings and furnishing, will be selected to enhance the participant’s perception of reality [34]. The video vignettes will depict dyads scenarios communicating across three stages of a cancer trajectory, with each stage introducing considerations for completion of different sections of an ACP (Table 2). Professional actors will be sourced from known professional college and university sources, and a pilot video will be created before the filming of the final videos. The video vignettes will be circulated to a multidisciplinary team for validation and approval and further editing before the final video intervention is created.

**Table 2 Tab2:** Predicted scenarios depicted in the video decision support tool

	Cancer stage	Values conversation depicted	ACP outcomes encouraged
**Vignette 1** **Early cancer diagnosis**	Early diagnosis, good performance status	Active treatment to preserve life at any cost	Appointment of a Medical Treatment Decision Maker and Support Person
**Vignette 2** **Living with serious illness**	Progressive metastatic disease, deteriorating performance status	Sustaining a reasonable quality of life through illness. Reflection of values and reprioritization of life choices	Completion of Values Directive. Consider when to discontinue cancer treatments / accept or refuse treatments based on acceptable quality of life
**Vignette 3** **Approaching the end of life**	Advanced metastatic disease, increased dependence	Effects of progressive frailty on quality of life despite active treatment. Reflection of meaningful relationships and EOL values	Completion of Instructional Directive. Discuss cardiopulmonary resuscitation, invasive/life-prolonging interventions, preferred place of death, contingencies e.g. funeral plans, spiritual needs.

### Study procedures

The study procedure is shown in Fig. 1. Participating clinicians will screen patients for eligibility, and interested eligible patients will be asked to nominate a participating caregiver. Eligible dyads will be informed verbally and in writing about the study and will be invited to meet with a research facilitator in their own homes or an allocated room in the hospital at an assigned date and time.

**Fig. 1 Fig1:**
[figure not shown]
Study procedure

Patients and caregivers will be consented individually by the research facilitator and will complete individual baseline pre-questionnaires (Supplementary file). Participants will then be randomised as dyads to either the UC or VDST arm. All participants will be advised that participation is voluntary, they may withdraw at any time, and that all information gathered will be treated in the strictest confidence. Patients and caregivers will also be advised that non-participation will not affect their care or their choice to complete an ACP.

Patients from both groups will be advised to discuss their completed ACP with their general practitioner or treating specialist to clarify any questions. The completed ACP will have to be signed, witnessed and returned with the post-questionnaire in a stamped return envelope. Participants will be advised to return the questionnaires even if they choose not to complete the ACP. Participants will receive two telephone call prompts at two-week intervals on completion of the intervention as a reminder to return the completed documents. Returned ACP’s will be scanned into the hospital’s electronic record system, and a copy returned to the patient.

### Sample size and power

Based on the primary outcome of the completion of ACP documentation and assuming a completion rate of around 37% for the control group, with a total of 86 participants/dyads (43 per group) we will be able to show a significant improvement to 67% completion for the VDST group (power of 80%, two sided 5% significance level). Assuming an estimated dropout rate of 30%, recruitment of 112 dyads will be required. Based on previous published studies, we felt that a sample of this size would give us sufficient methodological experience to conduct a subsequent fully powered study [12].

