### Quality standards

#### Randomization and blinding

Randomization occurs after completion of baseline assessments. An independent randomization administrator will complete randomization at the individual level using a computer-generated random number sequence in blocks of 6 in 1:1 ratio and with concealed allocation using numbered envelopes. The nature of the intervention makes it impossible to blind study participants. Treatment group assignments will therefore be non-blinded, but outcome assessors will be blinded to allocation.

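### The target of 112 dyads adds 30% to 86 instead of dividing by 0.70, so at the plan's own dropout rate about 39 per group remain and power is about 77%, not 80%

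*Protocol article*

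**What the plan says.** The sample size is tied to the primary outcome: "Based on the primary outcome of the completion of ACP documentation". The inputs are a control rate ("assuming a completion rate of around 37% for the control group"), a target rate ("significant improvement to 67% completion for the VDST group") and the error rates ("power of 80%, two sided 5% significance level"). From these the section derives its evaluable number: "with a total of 86 participants/dyads (43 per group) we will be able to show a significant improvement to 67% completion".

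The next sentence turns that number into a recruitment target: "Assuming an estimated dropout rate of 30%, recruitment of 112 dyads will be required". The article gives no other dropout figure and no other way of allowing for dropout. Allocation is equal between the arms (Randomization and blinding).

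**The concern.** A dropout rate is a fraction of those recruited. To be left with 86 dyads after losing 30%, the 86 must be divided by the fraction retained, 0.70. The printed target instead looks like 86 with 30% of itself added on, which always gives too small a number.

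If so, the trial would fall below its required 43 per group at exactly the dropout rate it planned for, and the 80% power on the primary outcome would not be reached. The Limitations section itself expects substantial attrition in this population, so the allowance is likely to be used. The article also presents the trial as groundwork for a larger study, which could inherit the same step.

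**Working it through.** **Inputs**, all from the Sample size and power section except the allocation ratio (Randomization and blinding):

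- control rate p1 = 0.37; VDST rate p2 = 0.67; difference 0.30; mean rate 0.52
- two-sided 5% level, z = 1.960; 80% power, z = 0.842
- 1:1 allocation
- 30% dropout; 112 dyads recruited

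**Step 1. Reproduce the evaluable number.** Normal approximation with pooled variance under the null and no continuity correction:

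n per group = [1.960 × √(2 × 0.52 × 0.48) + 0.842 × √(0.37 × 0.63 + 0.67 × 0.33)]² / 0.30²

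= [1.960 × √0.4992 + 0.842 × √0.4542]² / 0.09

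= [1.385 + 0.567]² / 0.09 = 42.3, rounded up to 43.

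That is 86 in total, as printed. Power at 43 per group is 80.6%. The plan's figure is reproduced exactly, so this formula is a fair basis for the later steps.

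**Step 2. Try to reproduce the recruitment target.**

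| Method | Calculation | Result |
|---|---|---|
| Add 30% to the evaluable number | 86 × 1.30 | 111.8, so 112 (the printed figure) |
| Divide by the fraction retained | 86 / 0.70 | 122.9, so 123; 124 for equal arms |

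The gap is 123 − 112 = 11 dyads, or 124 − 112 = 12. Rounding cannot account for it.

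**Step 3. What 112 delivers at 30% dropout.** 112 × 0.70 = 78.4, so about 78 dyads, or 39 per group instead of 43.

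**Step 4. Power at 39 per group**, same formula:

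z = [0.30 × √39 − 1.960 × √0.4992] / √0.4542 = (1.873 − 1.385) / 0.674 = 0.725, which gives power of 76.6%.

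Other methods, at both sample sizes:

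| Method | 43 per group | 39 per group |
|---|---|---|
| Pooled normal approximation | 80.6% | 76.6% |
| Arcsine approximation | 80.7% | 76.8% |
| Exact power of the uncorrected chi-square test | 79.9% | 77.8% |
| Unpooled normal approximation | 83.1% | 79.4% |

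The unpooled formula comes close to 80% at 39 per group, but it gives 83.1% at 43 and so does not fit the plan's own pairing of 80% with 43. The three methods that do fit give 76.6% to 77.8%.

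**Step 5. Detectable effect.** With control at 37% and 80% power, the detectable VDST rate is 66.8% at 43 per group and 68.2% at 39 per group.

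**Step 6. Dropout that 112 covers.** 1 − 86/112 = 0.232, or 23.2%.

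**The case against.** The arithmetic is hard to contest; the case on the other side is about how much it matters.

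- **The loss is small.** Power falls by about 4 points on the plan's formula and by about 2 on the exact calculation. The detectable rate moves by little more than one percentage point. The design, the conduct and the primary comparison are unaffected. This stands.
- **The inputs are approximate.** The control rate and the dropout rate are both given as estimates, and 112 is enough if dropout stays at or below about 23%. This is true, but the error lies in the step from the stated 30% to the stated 112, not in the choice of 30%.
- **The trial calls itself exploratory and a pilot**, and the section also justifies its size by the methodological experience to be gained. A pilot may well accept 77% power. But the section makes a formal power claim on the primary outcome and derives its recruitment number from it, so the numbers should agree.
- **Dropouts might still count in the analysis.** Under Study procedures the completed document is posted back with the post-questionnaire, and the article does not say whether a dyad that returns nothing is missing or a non-completer. If non-returners were counted as non-completers, all 112 dyads (56 per group) would be analysed and 77% would not apply. Power would be about 90% if the 37% and 67% already include non-returners, and lower than 77% if they do not. This does not rescue 112, because inflating for dropout treats lost dyads as absent from the 86. It does mean that the 77% should be printed with its condition.

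**Conclusion.** The point holds. The 86 evaluable dyads are correct and so is the 80% power attached to them. The recruitment target is wrong for the stated dropout: 112 does not preserve 86 after a 30% loss. It leaves about 78 dyads, 39 per group, with power of about 77% (76.6% to 77.8% by the methods consistent with the plan's own figure).

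The conclusion rests on the plan's rates of 37% and 67%, an uncorrected two-sided 5% test, dropout spread evenly over the arms, and no primary outcome data from lost dyads. The last of these is what the plan's own dropout allowance implies. The consequence is modest and does not undermine the design, but the statement concerns the primary outcome and is wrong as written.

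**What to change.** Correct the dropout sentence in Sample size and power in one of two ways.

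1. **Keep 112 and restate the power.** Suggested wording: *With 112 dyads recruited and 30% dropout, about 78 dyads (39 per group) would be evaluable and power would be about 77%, assuming that dropouts provide no primary outcome data; 80% power is retained if dropout does not exceed 23%.*
2. **Keep 80% power and 30% dropout and print 124** (62 per group). Check: 124 × 0.70 = 86.8, which covers the 86 needed.

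The first option costs one sentence and a slightly less favourable power figure, with no extra participants. The second costs 12 more dyads. For an exploratory trial the first is adequate.
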